### 2.14 Auditing

To ensure data integrity and consistency, the principal investigator will 
conduct weekly reviews of the CRFs and complete the estimation forms. To maintain 
consistency, research records in both paper and digital formats will be verified 
every two weeks. Any discrepancies identified will be thoroughly documented and 
discussed during research team meetings to facilitate timely corrective actions. 
These checks will be conducted throughout the entire study period, including 
during the therapy and 6-month follow-up assessment period.

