### 2.3 Randomization 

Randomization will be performed by a statistician who does not take part in the 
study. All eligible participants will be allocated into four groups using a 
computer-generated random number table. Each assigned a specific group number: 
HD-tDCS + CCRT (Group 1), HD-tDCS (Group 2), CCRT (Group 3), and control (Group 
4). For the randomization process, personnel employed Microsoft Excel 2019 
software (Microsoft Corp., Redmond, WA, USA) to enter 48 participants into a spreadsheet, assigning each a unique 
identifier ranging from “1–48”. They then used the “=RAND()” function to 
generate a random number for each assigned number. Subsequently, these random 
values were fixed using the “Paste Special” dialog box. Following this, the fixed 
random values were sorted in descending order. The sorted numbers were then 
divided into four groups, each comprising 12 numbers, resulting in a total of 48 
numbers. This procedure effectively randomized the 48 patients into four groups, 
with each group consisting of 12 individuals. Once the randomization scheme was 
established, it was secured in opaque envelopes, which were opened sequentially 
according to the order of participant enrollment. The allocation scheme within 
each envelope determined the group assignment for each patient. This method 
ensured that study personnel could not compromise the randomization process by 
having prior knowledge of the randomization scheme. The progression of 
participants through the screening, randomization, therapy, and follow-up stages 
is illustrated in Fig. 2.

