### 2.4 Blinding

Throughout the study period, both participants and evaluating psychiatrists 
remained blinded. In implementing blinding procedures, we will adhere to these 
considerations and measures. The specific group assignments of patients will be 
disclosed only to the principal investigator. Patients were unaware of the 
details of allocation sequences and were explicitly instructed not to discuss 
with each other any aspects of group allocation, received therapies, 
questionnaire completion, or other experimental procedures. Participants will 
keep unaware of the allocation sequences and will be explicitly instructed not to 
discuss any aspects of group allocation, receive therapies, questionnaire 
completion, or other experimental procedures. To minimize potential interference 
with blinding by therapy personnel, we will employ four distinct therapy groups, 
each responsible for implementing their respective therapies. Each group was 
informed only of their own protocol and had no knowledge of group allocation 
details or the therapy plans of other groups. Communication between groups 
regarding specific therapy content will be strictly prohibited. During the 
experimental phase, the principal investigator will provide each group with the 
specific protocol for their corresponding group, after which each group will 
implement the therapies for their assigned patients. During the outcome 
measurement phase, personnel responsible for data collection and analysis will 
keep blinded to group allocation and specific therapy. The principal investigator 
implemented a “two-stage unblinding” procedure. Once the data was locked, the 
initial unblinding was conducted, dividing the data into Groups 1–4 without 
disclosing their actual relationships or true assignments. The unblinding will be 
conducted after the data analysis is completed, clearly indicating the specific 
group representations of 1–4.

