### 2.10 Data Collection and Management

The assessment and examination related to the study scales will be conducted by 
clinical physicians who are external to the experiment and remain blinded to the 
study content. Outcome data collection will be managed by dedicated personnel, 
also external to the experiment, and will be systematically recorded in 
electronic Case Report Forms (CRFs). To ensure patient confidentiality, patient 
identification numbers will be utilized during data entry. The collected data 
will be transferred to a secure database for storage. After all data collection 
is completed, specialized analysts will conduct. Access to the data will be 
restricted exclusively to the principal investigator, data collectors, and 
analysts, and no modifications or exports will be permitted without 
justification. As patients will undergo follow-up and re-evaluation six months 
post therapy, they will be contacted and reminded via telephone, email, social 
media, and other communication methods at the appropriate time. During this 
period, no one except the principal investigator, data collectors, and analysts 
will be allowed to access, view, modify, or export the data without cause. Since 
patients will be followed up and re-evaluated six months after the ends, we will 
contact and remind them via phone calls, emails, social media, and other means at 
that time. During the data collection phase, participants who report significant 
changes in their antipsychotic medication regimen within the 6-month follow-up 
period will be identified and documented. Data from these participants will be 
included in all analyses up to the T2 time point, but will be excluded from the 
primary analysis of the T3 (6-month follow-up) data to prevent confounding the 
primary study outcomes.

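### The principal investigator knows every allocation and also reviews the unlocked CRFs weekly, which weakens the blinding of data handling before lock

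*Protocol article*

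**What the plan says.** Four sections of the protocol article bear on this.

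- **2.3 Randomization.** "Randomization will be performed by a statistician who does not take part in the" study. Assignments sit in opaque envelopes opened in order of enrolment.
- **2.4 Blinding.** A patient's specific assignment is "disclosed only to the principal investigator". During the experimental phase "the principal investigator will provide each group with the" protocol for its own arm. Participants, evaluating psychiatrists and those who collect and analyse data are to stay blinded. The data are split into coded groups only after lock, and the codes are explained only after the analysis.
- **2.10 Data Collection and Management.** External blinded physicians rate the scales, and dedicated external personnel record outcomes in electronic CRFs. Data access is "restricted exclusively to the principal investigator, data collectors, and" analysts, and changes or exports need justification. The section then repeats the restriction: "During this period, no one except the principal investigator, data collectors, and analysts" may access, view, modify or export data without cause.
- **2.14 Auditing.** The principal investigator will "conduct weekly reviews of the CRFs and complete the estimation forms". On timing: "These checks will be conducted throughout the entire study period, including" both the therapy and the six-month follow-up periods. Discrepancies are documented and "discussed during research team meetings to facilitate timely corrective actions".

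**The concern.** The two-stage unblinding in Section 2.4 has one purpose: nobody should be able to relate arm to outcome while the data can still change. Section 2.14 assigns a regular pre-lock review of the CRFs to the one study role that Section 2.4 says is told the assignments. A reviewer who knows the arm may, without intending to, query an unexpected value in one arm and pass over the same value in another. Such differential checking leaves no trace in the final data set.

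It matters more here than in a sham-controlled trial. Group 4 receives no sessions (Section 2.1), and the Discussion lists the absence of sham controls as a limitation. Patients and therapists can see what is delivered, so blinded rating and blinded data handling carry much of the protection against bias. No data monitoring committee is planned (Section 2.12), and Section 2.14 describes the only routine data checks in the article.

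**Working it through.** The plan gives no figure on this point and none is needed. The check sets the passages side by side.

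1. **Who knows the arm before lock?** The principal investigator, by Section 2.4, for all patients. Each therapy team knows the treatment it delivers. The outside statistician of Section 2.3 generates the sequence and may also hold it.
2. **What does the principal investigator see before lock?** Section 2.10 puts outcome data in the CRFs and gives this role data access. Section 2.14 adds a weekly CRF review through therapy and follow-up, which is before lock.
3. **Can the two be linked?** Section 2.10 uses patient identification numbers at data entry, for confidentiality. Nothing says the allocation record held by the principal investigator uses a different number, so coding by patient number is no stated barrier.
4. **Can the review affect the data?** Section 2.14 sends discrepancies to team meetings for corrective action. It does not say who makes the correction. The route therefore runs from an arm-aware reviewer to a query, to a team discussion, to a possible change.
5. **Is a safeguard stated for this step?** Section 2.10 requires justification for changes, but names no blinded person to judge it. Section 2.14 adds a two-weekly verification of paper and digital records, again without saying that whoever does it is blinded.
6. **What are the estimation forms?** The term appears once and is not defined. If they are audit or data-quality forms, the issue is unblinded pre-lock review, as in steps 2 to 5. If they hold outcome ratings, they conflict directly with Section 2.10, which gives the scales to external blinded physicians. The heading of Section 2.14 and its stated purpose of data integrity favour the first reading, but the text does not settle it.
7. **Are the T3 exclusions protected?** Section 2.10 removes patients with significant antipsychotic changes from the primary T3 analysis. It is written in the passive: no role is named as deciding what is significant, and blindness to arm is not stated.

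Steps 1 to 5 stand on the text alone. Steps 6 and 7 identify wording that leaves a related question open.

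**The case against.** The strongest reply is that nothing here is a literal contradiction. Section 2.4 lists who is blinded and openly excepts the principal investigator. Section 2.10 names that role separately from data collectors and analysts. A CRF review by an unblinded person unblinds none of the roles promised blinding. External physicians score the scales, external personnel record them, changes need justification, and the groups stay coded until the analysis is done. The primary outcome is also a battery of cognitive tests (Section 2.9), which leaves less room for steering through a CRF query than a clinician's rating would.

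Most of this stands, and it rules out several stronger readings that a reader might draw:

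- *That the blinding of outcome data is undone.* It is not. The raters, recorders and analysts remain blinded as stated.
- *That blinded data handling is the only real protection in an unmasked trial.* Blinded external scoring is a separate protection and is intact.
- *That the principal investigator decides who leaves the T3 analysis, or makes the corrections.* No section says so.
- *That the access rule permits changes.* Its wording is a restriction.

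What the reply does not answer is why the two-stage unblinding withholds even coded groups until lock when a role that already knows the real groups reviews the unlocked records every week. The duty is assigned in the text; this is not a detail that a fuller document would merely complete.

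**Conclusion.** The point holds in limited form. Giving one role knowledge of all assignments, data access, weekly pre-lock CRF review and completion of undefined forms weakens the blinding of data handling before lock. It does not touch the scoring of outcomes.

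The size cannot be stated as a number. Any figure would need an assumed count of selectively handled records and an assumed distance of each from its arm mean, and the documents support neither. They show that the route is open, not that it would be used. The conclusion assumes that the CRFs reviewed include the outcome pages, as Section 2.10 implies, and that the principal investigator can match patient numbers to arms. It is a cheap improvement, not a flaw that invalidates the design.

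**What to change.** Separate knowledge of allocation from pre-lock review, using people already in the plan. Either of two changes does this.

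- **Option A (Sections 2.3 and 2.4).** Keep the allocation list with the outside statistician and release the sealed envelopes only to the therapy teams. Since the envelopes are prepared beforehand, this need not draw the statistician into running the trial. The teams would receive their protocols without the principal investigator knowing which patient is in which arm. The principal investigator then stays blinded until lock and can keep the CRF review.
- **Option B (Section 2.14).** Leave allocation as it is, and give the pre-lock CRF review and form completion to an existing blinded team member. This should not be the person who entered the data, because checking one's own entries is a weak audit.

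Under either option, whoever checks outcome pages blind should not also check the adverse-reaction pages. Section 2.13 makes that form specific to HD-tDCS, so it can reveal the arm.

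Two sentences should be added in any case. Section 2.14 should define the estimation forms and state that they contain no outcome ratings by an unblinded person. Section 2.10 should state that T3 exclusions for medication changes are decided blind to arm and before lock.

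The cost is protocol wording and a small reassignment of tasks. Under Option A the principal investigator also gives up some direct oversight of allocation.

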### 2.15 Protocol Modifications

All significant amendments to the study protocol will first be presented to the 
Ethics Review Committee of the Second Affiliated Hospital of Xinxiang Medical 
University. Once approved, these changes will be documented in writing to all 
relevant parties and properly recorded on the Chinese Clinical Trial Registry 
platform.

### 2.16 Dissemination Policy

Before the first patient is enrolled in the trial, relevant trial information 
will be published on the website of the Chinese Clinical Trial Registry. We are 
devoted to making all research findings accessible to the public. These findings 
will not only be presented and deliberated at international conferences but also 
submitted for publication in peer-reviewed academic journals.

## 3. Expected Results

This study will evaluate between-group differences at specific time points and 
within-group changes over time for both primary and secondary outcomes. We 
hypothesize that MRI-guided HD-tDCS combined with CCRT will result in more 
significant improvements compared to those receiving HD-tDCS or CCRT alone. 
Following four consecutive weeks of treatment, it is anticipated that the 
combined group will exhibit amelioration of prefrontal dysfunction, as measured 
by MRI, and demonstrate significantly elevated expression levels of BDNF and 
GDNF.

## 4. Discussion

To the best of our knowledge, this prospective, randomized, double-blind, 
controlled trial represents the first to investigate the synergistic effects of 
MRI-guided HD-tDCS targeting mPFC and CCRT on cognitive dysfunction in 
schizophrenia. First, we will employ MRI-guided HD-tDCS to ensure that the 
electrical current is confined to the targeted region of the mPFC, delivering 
more precise and focused stimulation. Further, we present a randomized, 
double-blind, controlled design to investigate the potential role of cognitive 
improvement in schizophrenia through the MRI-guided HD-tDCS and CCRT. Second, 
cognitive impairment is the core symptom of schizophrenia, which not only 
severely affects the overall quality of life of patients but also places 
significant burdens on their caregivers [53]. Herein, this study will evaluate 
not only the short-term effects in schizophrenia, but also address the long term 
effects after six months of follow-up. Third, multiple objective methods will 
contribute to a comprehensive understanding of the mechanisms of HD-tDCS and CCRT 
in schizophrenia. We hypothesize that this combined group will exhibit more 
pronounced improvements compared to those receiving either HD-tDCS or CCRT alone. 
If confirmed, the study will introduce an efficient method for addressing 
cognitive impairments, thereby assisting clinical psychiatrists in selecting 
individualized therapy strategies and potentially improving patients’ quality of 
life and social functioning.

In this study, we propose MRI-guided HD-tDCS targeting the mPFC to ameliorate 
cognitive deficits in patients with schizophrenia. The mPFC is intrinsically 
associated with memory and decision-making functions in humans [54]. Individuals 
with schizophrenia often exhibit pronounced functional abnormalities in the mPFC, 
which may impair their cognitive control capabilities and lead to reduced 
performance on complex tasks [55]. Research indicates that HD-tDCS targeting the 
mPFC can enhance activation in the insula while decreasing activation in the 
amygdala, resulting in improvements in attention, working memory, and 
probabilistic learning [56]. Accordingly, HD-tDCS targeting the mPFC has been 
shown to enhance decision-making behaviors under conditions of low outcome 
controllability, thereby promoting more adaptive behavioral performance [57]. The 
specific mechanisms of tDCS involve the activation of N-methyl-D-aspartate 
receptors and the upregulation of BDNF expression, both of which contribute to 
the enhancement of synaptic plasticity. Additionally, tDCS influences the release 
of neurotransmitters. The modulation of glutamate and glutamine release can 
influence neuronal excitability, thereby facilitating the processes of learning 
and memory formation [58, 59, 60]. This modulation not only contributes to short-term 
cognitive improvements but may also lead to long-term cognitive enhancements 
through the mechanism of long-term potentiation (LTP) [55]. Consequently, 
MRI-guided HD-tDCS targeting mPFC emerges as a promising and precise strategy for 
enhancing cognitive function at an individual level.

Interestingly, CCRT has been shown to ameliorate cognitive impairments by 
modulating neural activity within the mPFC [61]. CCRT has been observed to 
increase brain activity in the mPFC, parietal cortex, insula, caudate nucleus, 
and thalamus [62]. Recent studies have demonstrated that following CCRT, the 
amplitude of low-frequency fluctuations (ALFF) in the mPFC was significantly 
increased, while ALFF in the brainstem was significantly decreased in patients 
with schizophrenia [63]. Additionally, neuroimaging studies have revealed that 
CCRT may enhance cognitive function in schizophrenia by increasing the integrity 
of the anterior corpus callosum white matter fibers, thereby improving the 
efficiency of information transfer in the bilateral mPFC [64]. CCRT has been 
shown to significantly elevate GDNF levels in patients [42]. These findings 
indicate that CCRT may facilitate cognitive enhancement by modulating neural 
activity in the mPFC and regulating neurotrophic factor levels. In conclusion, 
CCRT presents a potentially effective therapeutic strategy for enhancing 
cognitive function in individuals with schizophrenia through computerized, 
individualized training and associated mechanisms.

The integration of HD-tDCS and CCRT offers a valuable adjunct to conventional 
antipsychotic therapies. Patients with schizophrenia often require prolonged use 
of antipsychotic medications, which can result in side effects such as 
extrapyramidal symptoms, endocrine disturbances, and metabolic issues. By 
reducing dependence on pharmacological therapies, HD-tDCS and CCRT may help 
mitigate these adverse effects, thereby enhancing patients’ overall quality of 
life. Additionally, a notable advantage of this combination is its convenience 
and cost-effectiveness. HD-tDCS devices are relatively portable and 
user-friendly, rendering them suitable for extensive application use in home 
settings. This methodology is supported by a recent quantitative summary 
confirming the efficacy, safety, and tolerability of home-based tDCS [65]. CCRT 
content can be delivered via online platforms, enabling patients to manage their 
treatment independently at home and thereby minimizing the necessity for frequent 
hospital visits. Consequently, the integration of HD-tDCS with CCRT not only 
offers economic advantages but also enhances the convenience of treatment. This 
synergy is likely to improve patient adherence and increase the flexibility of 
therapeutic interventions. Due to its affordability and accessibility, this 
combined approach is well-suited for community health centers, rehabilitation 
facilities, and home-based care. Future studies should focus on determining the 
optimal parameters for HD-tDCS and CCRT, such as current intensity, stimulation 
duration, and specific CCRT task types, as well as the development of 
standardized protocols for their implementation in clinical practice.

More importantly, this study will utilize structural and functional MRI to 
assess the modulatory effects of HD-tDCS in conjunction with CCRT on brain 
activity in individuals with schizophrenia. By measuring blood oxygen 
level-dependent signals, fMRI provides high spatial resolution insights into 
neural activity changes in specific brain regions and elucidates the dynamic 
interactions within large-scale brain networks. This imaging technique 
facilitates the observation of neural activity in targeted brain regions, 
enabling correlations with cognitive functions and predictions of therapeutic 
outcomes. Interestingly, the mPFC, part of the default mode network, shows 
increased activity in patients during working memory tasks [66]. Previous fMRI 
studies examining spontaneous neural activity have demonstrated that functional 
connectivity between the mPFC and the left orbitofrontal cortex in schizophrenia 
is positively correlated with performance on the DST and other cognitive 
assessments [67]. We hypothesize that the combined approach will result in 
altered activity within the mPFC, potentially correlating with cognitive 
improvements. Collectively, multimodal MRI approaches have deepened our 
understanding of the possible mechanisms of HD-tDCS and CCRT in schizophrenia, 
which is essential for precise medicine with significantly improved outcomes.

This study also focuses on the potential role of BDNF and GDNF in enhancing 
cognitive function through the combined application. BDNF, the most ubiquitously 
distributed neurotrophic factor in the brain, is integral to synaptic plasticity 
and learning processes, with its increased expression positively affecting LTP 
and memory formation [68, 69]. In patients with schizophrenia, plasma BDNF levels 
have been shown to change in parallel with cerebrospinal fluid BDNF levels, 
indicating that peripheral measurements may serve as reliable markers of central 
BDNF status [43]. Furthermore, studies have shown reduced BDNF levels in 
individuals with schizophrenia, which tend to increase following therapeutic 
interventions [40]. GDNF is essential for the nervous system, as it supports the 
survival, differentiation, and function of dopaminergic neurons, thereby 
maintaining normal brain activity [70]. A meta-analysis has demonstrated 
significantly lower GDNF levels in patients compared with healthy controls, with 
antipsychotic medication restoring these levels [71]. Based on these findings, it 
has been suggested that BDNF and GDNF may serve as potential biomarkers and 
predictors of therapeutic response in schizophrenia. Monitoring GDNF levels may 
facilitate the optimization of personalized therapeutic strategies for 
schizophrenia. Consequently, this study aims to examine serum alterations in 
BDNF/GDNF pre- and post-intervention to investigate their potential role in 
mediating cognitive improvements, thereby providing biological evidence for the 
combined therapy.

It is important to note that variables such as illness duration and long-term 
antipsychotic treatment may influence treatment efficacy. Research suggests that 
chronic antipsychotic use can induce adaptations in dopaminergic pathways, 
including upregulation of dopamine transporters, decreased firing rates of 
dopamine neurons, and decreased synaptic vesicle release [72]. Additionally, 
antipsychotics may affect synaptic function by modifying the levels of 
postsynaptic density protein 95 and altering dendritic spine density [73]. A 
longitudinal study investigating first-episode schizophrenia patients revealed 
that after two years of pharmacological treatment, there were observed increases 
in basal ganglia and white matter volumes, accompanied by widespread cortical 
thinning [74]. Individuals with chronic, untreated schizophrenia exhibit more 
pronounced progressive deterioration of brain structures—such as reductions in 
gray matter volume, diminished white matter integrity, and disrupted brain 
network connectivity—compared to those who have been recently diagnosed or 
treated [75]. These findings suggest that the complex interplay between the 
pathophysiological processes of the disease and its pharmacological management 
may influence the therapeutic efficacy of both HD-tDCS and CCRT. Future research 
should incorporate subgroup analyses based on illness duration to specifically 
investigate how these factors may moderate the interaction between HD-tDCS and 
CCRT.

This study still has some limitations. Firstly, the relatively small sample size 
might influence the statistical power and limit the generalizability of the 
outcomes. Future research should consider increasing the sample size to enhance 
statistical robustness. Secondly, the absence of a double-sham control group, 
which would receive both sham HD-tDCS and a sham version of CCRT, complicates the 
ability to definitively differentiate between specific therapeutic effects and 
potential placebo effects. Additionally, the lack of corresponding sham controls 
for the HD-tDCS-alone and CCRT-alone groups constrains our capacity to accurately 
assess the independent contributions of each monotherapy. Thirdly, we intend to 
collect resting-state fMRI data, which could not provide task-specific 
information. Future study will employ task state fMRI to reflect the fMRI images 
of the brain when performing specific tasks. Finally, the mechanisms underlying 
the combined therapy remain relatively unexplored, particularly regarding how 
these two modalities synergistically enhance cognitive function through specific 
pathways. This necessitates further comprehensive research to elucidate these 
mechanisms.

This study protocol establishes an important theoretical framework for exploring 
the combined therapy and provides guidance for future research. Using MRI-guided 
HD-tDCS targeting mPFC will enhance the development of individualized therapies 
for schizophrenia. Findings from multimodal neuroimaging and blood biomarkers 
could uncover the mechanisms of combining MRI-guided HD-tDCS with CCRT for 
schizophrenia and contribute to develop more individualized approaches. As a 
result, this integrated therapeutic strategy holds significant promise for 
translation into clinical practice.

